### Plans to promote participant retention and complete follow-up {18b}

All efforts will be made to retain all participants in the study. As they are also part of the earlier ENDIRA study, there is a good rapport with the study group, local self-government, and frontline health workers. Loss to follow-up may result from migration to their children’s places of living or death or for other reasons. The characteristics of the patients who drop out will be recorded and compared to those who are in the study.

### Data management {19}

As the data is collected through the SHRADDHA app, the data will be exported to excel and checked for completion each day. According to the data collected, feedback, and monitoring will be done to ensure correct and complete entries. Duplicate entries will be checked for and removed.

### Confidentiality {27}

The data of the patients will be anonymized, and each patient will be assigned a unique id. From the app de-identified anonymized data will be stored in Excel. This will be stored confidentially before, during, and after the trial.

### Plans for collection, laboratory evaluation, and storage of biological specimens for genetic or molecular analysis in this trial/future use {33}

In this study, blood samples will be collected to assess random blood sugar and HbA1c. These tests are done using point-of-care devices. The blood samples will not be stored in the current trial.

## Statistical methods

### Statistical methods for primary and secondary outcomes {20a}

Several models will be run to test for the main outcomes, implementation outcomes, and related research questions. Mixed linear and logistic effects models as appropriate will be used to identify differences between the groups (ASHA, ASHA and m-health, m-health, control group), where random effects will be used for the clusters and fixed effects will be used for effects of ASHA workers and of m-health. The primary dependent variable in the models will be change in adherence measured by the Morisky scale. Models will also be fitted for the secondary outcomes such as change in blood pressure, random blood sugar, Hba1c levels, and quality of life. Subsequently, covariates such as age, sex, and co-morbidities will be added to the models to adjust for potential confounders.

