### Objectives {7}

#### Primary objective

To assess the effectiveness of using m-health and community health worker-led interventions for improving adherence to drugs in patients with cardiovascular disease using m-health and community health worker intervention individually and in combination in comparison to control group.

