### Trial design {8}

It is a 2 × 2 factorial design trial applying two interventions individually and in combination with a 1:1 allocation ratio. Two interventions are applied individually and in combination: (i) ASHA-led medication adherence initiative comprising of home visits, and (ii) m-health intervention using reminders and self-reporting of medication use. This design will lead to four potential experimental conditions: (i) ASHA-led intervention, (ii) m-health intervention, (iii) ASHA and m-health intervention combination, (iv) standard of care.

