*Sample size*: Sample size was estimated assuming an improvement of 10% in medication adherence at the end of a 6-month period in either m-health or community health worker-led intervention compared to control group. This 10% improvement will lead to an effect size of 0.4 units in medication adherence through m-health or community health worker-led intervention and an effect size of 0.8 units in combined intervention (m-health and community health worker-led intervention) compared to the control group. The 10% was an assumption considering that large differences are not possible in a community setting and was based on another community-based study which has also used 10% improvement of adherence score [24].

To observe a difference of 0.4 units in the medication adherence between study groups, with a standard deviation of 1.8, 5% level of significance (adjusted for multiple comparison) and 80% power, the sample size needed will be 238 participants in each of the study groups. After accounting for a design effect (cluster effect) and 10% attrition, the number of participants required per group will be 393, a total of 1572 participants.

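### Section {20a} promises differences among four groups but names only ASHA and m-health as fixed effects; read literally, this additive model does not match the alone-versus-control contrasts of the primary objective

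*Protocol article*

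**What the plan says.** The Primary objective asks for the effect on adherence of "using m-health and community health worker intervention individually and in combination in comparison to control group". Outcomes {12} repeats the idea, with standard of care as the comparator.

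Trial design {8} describes the structure: "It is a 2 × 2 factorial design trial applying two interventions individually and in combination with a 1:1 allocation ratio".

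The sample-size paragraph under Baseline study works with group contrasts against control. It takes 0.4 units for either intervention and "an effect size of 0.8 units in combined intervention". It states the error rate as a "5% level of significance (adjusted for multiple comparison"), with 80% power, SD 1.8 and 238 participants per group, raised to 393 for clustering and attrition.

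Statistical methods {20a} says that mixed models "will be used to identify differences between the groups (ASHA, ASHA and m-health, m-health, control group"), and continues in the same sentence that "random effects will be used for the clusters and fixed effects will be used for effects of ASHA workers and of m-health". The outcome is a change score: "The primary dependent variable in the models will be change in adherence measured by the Morisky scale". The section names neither a four-level arm factor nor an ASHA × m-health term.

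**The concern.** Four free group means need four parameters: an intercept, two main effects and an interaction. An intercept and two main effects supply three. A model with only the two named effects therefore forces the combined effect to equal the sum of the single effects. Each coefficient then averages an intervention's effect over the presence and absence of the other. That is a factorial main effect, whereas the objective asks for the effect of each intervention given alone against control.

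The two agree only if there is no interaction. The plan assumes this in its sample size (0.4 and 0.4 giving 0.8) without justifying it. Less than additive effects are plausible: both interventions give health advice and support medicine-taking in the same patients, and the adherence scale stops at 8.

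The alone-versus-control estimates, which would inform a choice between the two interventions, are at stake. So is the freedom to choose after seeing the data between two primary analyses that differ in target and in power.

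**Working it through.** **Inputs from the protocol article.** Sample-size paragraph: difference 0.4, SD 1.8, 80% power, 5% level, 238 per group, then 393; combined effect 0.8. Sequence generation {16a}: 18 subcenters in four groups, taken here as two groups of 5 and two of 4.

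**1. The plan's own figure.** For a two-group comparison, n per group = 2(z₁₋α/₂ + z₀.₈)²(SD/δ)².
- Two-sided 0.05: 2 × (1.960 + 0.842)² × (1.8/0.4)² = 318.
- Two-sided 0.05/3: 2 × (2.394 + 0.842)² × 20.25 = 424.

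The stated 238 does not follow from the stated inputs and lies below even the unadjusted 318. The step to 393 is matched by 238 × 1.5 × 1.1 = 392.7, where the design effect of 1.5 is back-solved because the article gives none.

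**2. What the two-term model estimates.** Let the group means relative to control be 0 (control), a (ASHA), b (m-health) and a + b + g (both), where g is the interaction. With equal groups, least squares gives:
- ASHA coefficient = [a + (a + b + g − b)]/2 = a + g/2
- m-health coefficient = [b + (a + b + g − a)]/2 = b + g/2
- sum of the two = a + b + g, the true combination-versus-control difference.

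**3. Numbers, with a = b = 0.40.** The values of g are illustrative; the document gives none. The ranges cover every allocation of 5, 5, 4 and 4 clusters to the groups, weighting cluster means equally.

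| True combined effect | g | Each coefficient, balanced | Range over 5/5/4/4 | Estimated combined effect, range |
|---|---|---|---|---|
| 0.8 | 0 | 0.40 | 0.40 | 0.80 |
| 0.6 | −0.2 | 0.30 | 0.29–0.31 | 0.59–0.61 |
| 0.4 | −0.4 | 0.20 | 0.18–0.22 | 0.38–0.42 |

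The error also runs the other way: g = +0.4 gives 0.60 per intervention in the balanced layout.

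**4. Precision and power, taking 238 as the effective number per group.**
- Alone versus control: SE = 1.8 × √(2/238) = 0.165. Since 0.4/0.165 = 2.424, power is Φ(2.424 − 1.960) = 68% at 0.05 and Φ(2.424 − 2.394) = 51% at 0.05/3.
- Additive-model coefficient (two groups pooled on each side): SE = 1.8 × √(2/476) = 0.117. Since 0.4/0.117 = 3.428, power is 93% at 0.05 and 85% at 0.05/3.
- Ratio of standard errors: 0.165/0.117 = 1.4.
- Interaction: SE = 1.8 × √(4/238) = 0.233. Power to detect |g| = 0.4 at 0.05 is Φ(1.714 − 1.960) = 40%.

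These powers treat the back-solved design effect as capturing all clustering and ignore the few degrees of freedom from 18 clusters, so they are optimistic.

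**The case against.** The strongest reply is that {20a} never says main effects only. The sentence first names all four groups as those to be compared, and the fixed-effects clause may only be saying which factors are fixed and which random. The section also foresees several models. This stands in part: the text is ambiguous, not expressly additive. But the clause is the only description of the fixed part, and the two effects it names cannot yield four free group differences.

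A second reply is that the literal model is unbiased under the additivity the sample size assumes. That is correct. The bias is conditional on an interaction, and its size here comes from illustrative values.

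Three stronger readings are tempting and should not be drawn.

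- A reader might infer that the trial cannot show whether the combination adds anything. All four groups are randomized and the combined group is named for comparison, so the data support that contrast. Even the two-term model estimates combination versus control nearly correctly.
- A reader might infer that there is no multiplicity rule. The sample-size paragraph says the 5% level is adjusted. The method is not named, but an article may leave that to the analysis plan.
- A reader might infer that the family-wise error exceeds 5%. That would require three unadjusted tests, which no section announces. Multiplicity in any case bears on error rate, not on what the model can estimate.

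**Conclusion.** The point holds as a mismatch between a stated model and a stated objective. Read literally, the fixed effects in {20a} target factorial main effects, while the Primary objective and the sample-size contrasts target each intervention alone, and the combination, against control. The discrepancy is half the interaction: 0.10 of a true 0.40 if the combined effect is 0.6, and 0.20 if it is 0.4. It is zero under exact additivity. These figures assume equal single effects of 0.40 and near-balanced groups.

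The choice also matters for power: at 5% unadjusted, about 93% for a pooled main effect and about 68% for an alone-versus-control contrast. The wording therefore needs settling before the endline data are analysed.

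**What to change.** Amend {20a} to state the following.

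- The primary model contains ASHA, m-health and ASHA × m-health (equivalently a four-level arm factor), with a random cluster effect.
- The primary contrasts are ASHA alone, m-health alone and the combination, each against standard of care, all taken from this model.
- The multiplicity adjustment already claimed in the sample size applies to these three contrasts, with the method named there or in the analysis plan.
- The interaction is reported with its confidence interval. It is not used as a gate for choosing the model, because power to detect an interaction of 0.4 is only about 40%.
- The two marginal main effects are kept as a secondary analysis, labelled as assuming no interaction.

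This changes wording only and needs no new data, but it has a price that should be disclosed with it. Alone-versus-control intervals are about 1.4 times wider than those from the additive model. At 238 effective participants per group, power for 0.4 at SD 1.8 is about 68% unadjusted and about 51% at 0.05/3, against the stated 80%. Reaching 80% would take 318 or 424 per group before inflation, or about 525 or 700 after the same factors of 1.5 and 1.1 (318 × 1.65 = 524.7; 424 × 1.65 = 699.6), against 393 planned. If the sponsor prefers the pooled main effects as primary, the objective should be reworded to say so and the no-interaction assumption stated.

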### Outcomes {12}

#### Primary, secondary, and other outcomes

The primary outcome is the adherence of patients as measured by Morisky adherence scale [21] at the beginning of the study, midterm, and at the end. The secondary outcomes include Quality of Life (EuroQOL) [22], blood pressure, random blood sugar, HbA1c among the cardiac patients with type 2 diabetes, mortality events, and other unintended outcomes will also be recorded. The analysis will include change from baseline. Adherence is chosen as the main outcome as the objective is to study the impact of the various interventions singly and in combination on adherence in comparison to standard of care. Various symptoms, such as dyspnea, fatigue, edema, difficulty sleeping, depression, and chest pain associated with CVD limits activities of daily life [23]. Therefore, it is important to measure the quality of life before and after the intervention. Metabolic control can result from better adherence to medication and a better awareness of the importance to adhering to medication. Therefore, meeting targets of blood pressure, blood sugar levels, and HbA1c will be considered as secondary outcomes.

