**Assessments**									
Baseline assessment	♦	♦							
Primary outcome									♦
Secondary outcome									♦

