### Methods for additional analyses (e.g., subgroup analyses) {20b}

Subgroup analysis will not be carried out. However, for the primary and secondary outcome variables, covariates such as age, sex, and co-morbidities will be considered as potential confounders in the mixed effect model analysis.

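### The first-line primary model analyses change in MMAS-8 without adjusting for baseline MMAS-8, which costs precision and leaves chance baseline imbalance in the estimate; the midterm measurement also needs reconciling with Table 1

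*Protocol article*

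**What the plan says.** **Model.** Statistical methods for primary and secondary outcomes {20a} sets the outcome: "The primary dependent variable in the models will be change in adherence measured by the Morisky scale". The Outcomes {12} text agrees: "The analysis will include change from baseline". The structure is a mixed model in which "random effects will be used for the clusters and fixed effects will be used for effects of ASHA workers and of m-health". Covariates come in a further step: "Subsequently, covariates such as age, sex, and co-morbidities will be added to the models to adjust for potential confounders". Methods for additional analyses {20b} repeats the same list: "covariates such as age, sex, and co-morbidities will be considered as potential confounders in the mixed effect model analysis". Baseline MMAS-8 appears in neither list, and no time term is named.

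**Allocation.** Sequence generation {16a} allocates 18 subcenters to four groups by random permutation and describes no stratification or balancing on baseline adherence. Recruitment {15} and Concealment mechanism {16b} place allocation after the baseline assessment.

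**Timing.** The Outcomes text measures the primary outcome "at the beginning of the study, midterm, and at the end". In Table 1 the row labelled "Primary outcome" is marked at close-out only. The sample size paragraph under Baseline study works from "assuming an improvement of 10% in medication adherence at the end of a 6-month period". Recruitment {15} plans an endline assessment in December 2024 and mentions no midterm one.

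**The concern.** MMAS-8 is a self-reported score from 0 to 8, and two readings months apart on one person are imperfectly correlated. An arm that happens to start low will tend to rise more, and an arm that starts high less, without any treatment effect. An unadjusted change score counts that movement as effect. With 4 or 5 subcenters per arm, such imbalance is easy to get by chance.

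The second cost is precision. Subtracting baseline fixes its coefficient at 1, when the data would usually support a smaller one, and the excess adds noise. The baseline score is measured before allocation, so it is a legitimate covariate, and the protocol already plans to collect it.

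The timing mismatch is smaller. Assessors are not blinded (Who will be blinded {17a}) and the outcome is self-reported, so a midterm reading with no assigned role should not be left undefined beside the primary result.

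**Working it through.** **Inputs.** From the sample size paragraph: difference 0.4, SD 1.8, 80% power, 5% level described as adjusted for multiple comparison, 238 per group before design effect and attrition. Assumed, because the document does not give it: correlation rho between baseline and endline MMAS-8, range 0.3 to 0.7. The document does not say whether SD 1.8 belongs to a single score or to change.

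**Step 1, the plan's own figure.** For two means, n per group = 2 × SD² × (z_alpha + z_power)² / difference². At two-sided 5% this is 2 × 3.24 × (1.960 + 0.842)² / 0.16 = 317.9, so 318. One-sided 5% gives 251; two-sided 0.05/3 gives 424. The stated 238 is not reproduced. That is a separate point and is not relied on here.

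**Step 2, variance ratio.** With equal variances at both times:

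- unadjusted change: 2 × SD² × (1 − rho)
- baseline-adjusted: SD² × (1 − rho²)
- ratio, adjusted to change: (1 + rho)/2, below 1 for every rho below 1

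For comparison, the endline score alone has variance SD², so change is noisier than endline alone whenever rho is below 0.5.

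**Step 3, numbers.** If 1.8 is the SD of a single score, at two-sided 5%, before clustering and without a multiplicity adjustment:

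| rho (assumed) | ratio | n per group, change | n per group, adjusted | power at 238, change | power at 238, adjusted |
|---|---|---|---|---|---|
| 0.3 | 0.65 | 446 | 290 | 53.5% | 71.9% |
| 0.5 | 0.75 | 318 | 239 | 67.9% | 79.9% |
| 0.7 | 0.85 | 191 | 163 | 87.9% | 92.4% |

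If 1.8 is instead the SD of change, 318 falls to 207, 239 and 271 at the same three values. The ratio does not depend on which reading is right; the absolute numbers do.

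**Step 4, effect of an imbalance.** Given a baseline difference d between two arms, the expected endline difference is the treatment effect plus rho × d. The expected difference in change is therefore the treatment effect minus (1 − rho) × d. Each unit of imbalance moves the change-score estimate by 0.70, 0.50 or 0.30 units in the opposite direction at rho 0.3, 0.5 and 0.7. As an illustration, an imbalance of 0.2, half the target difference, would move it by 0.14, 0.10 or 0.06 against a target of 0.4. This uses the individual-level slope; the slope between subcenter means may differ.

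**Step 5, time point.** Three places fit the end of the 6 months: the sample size basis, the close-out mark in Table 1, and the December 2024 endline in Recruitment {15}. One place, the Outcomes text, adds midterm. Neither the Outcomes text nor {20a} says which measurement is primary.

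**The case against.** - **The covariate list is open and the analysis plan is not shown.** This is fair: baseline MMAS-8 is unnamed, not ruled out. But {20a} adds covariates only after a first model, so even an unlisted baseline covariate would come in at the second step.
- **Change is a legitimate outcome.** This stands. In a linear model, change with baseline as a covariate gives the same treatment effect as endline with baseline as a covariate; only the baseline coefficient shifts by 1. The fault is the missing covariate, not the outcome.
- **Randomisation already protects against bias.** On average over randomisations, yes. A reader might infer that unadjusted change is a biased analysis; the concern is only with the imbalance realised in one draw of 18 clusters, and with precision.
- **The saving is not established for this trial.** Correct. The ratio is an individual-level figure on an assumed rho. The gap from baseline to endline is about 7 to 10 months on the Recruitment {15} dates, and up to about 13 on the Trial status start date, but neither tells us what rho is.
- **The primary time point is not open.** This stands. A reader might infer that midterm and endline compete as primary, but the sample size, Table 1 and the recruitment plan all agree on the end. What is left is a reconciliation.
- **The match with 238.** A reader might infer from the 239 at rho 0.5 that only a baseline-adjusted analysis fits the stated 238. It does not follow: unadjusted change gives the same figure at rho of about 0.63 (317.9 × 2 × 0.374 = about 238). The match also ignores the stated multiplicity adjustment; at 0.05/3 the adjusted figure at rho 0.5 is 424 × 0.75 = 318.

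**Conclusion.** The point holds in a limited form. The first-line primary model, as written, is an unadjusted change score, and adding baseline MMAS-8 would improve it. At the individual level the adjusted analysis has 65% to 85% of the change-score variance for rho between 0.3 and 0.7. That range rests on an assumed rho and on equal variances at the two times, and the gain in this cluster trial also depends on the correlation of subcenter means over time, which is not given. The direction does not depend on the value chosen: at the individual level the ratio is below 1 for any rho below 1. The timing issue is an inconsistency between the Outcomes text and Table 1, with endline the evident intent. Nothing here shows that the planned analysis is invalid.

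**What to change.** 1. In {20a}, state that the primary mixed model includes individual baseline MMAS-8 as a fixed covariate from the start, alongside the ASHA and m-health effects and the random cluster effect. Either change or the endline score may remain the outcome.
2. Do the same for the continuous secondary outcomes that have a baseline value: blood pressure, random blood sugar, HbA1c and quality of life.
3. Optionally add the subcenter mean of baseline MMAS-8, so that the between-subcenter slope can differ from the individual one. This costs one cluster-level degree of freedom out of a small supply (18 subcenters), so it is a judgement, not a requirement.
4. In the Outcomes text and in {20a}, name MMAS-8 at the end of the 6 months as the primary time point. Give midterm a stated secondary role and add it to Table 1, or delete it from the Outcomes text.

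The cost is analysis wording and at most one table entry. Items 1 to 3 need no new data, because the baseline score is already planned for collection before allocation.

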### Interim analyses {21b}

In this study, the intervention is done to improve the medication adherence through health education by ASHA workers, m-health, or both. Since the risk due to the intervention is minimal or none, interim analysis, and stopping guidelines have not been prescribed by the ethical committee and therefore there will not be any stopping guidelines.

